| Follow-up plan | 
Face to face interviews will be performed at baseline, Day7<math>\pm</math>2, Day14 (or hospital discharge) and Day90 <math>\pm</math> 7, and telephone interviews will be performed at the 12th month<math>\pm</math>14 days after randomization.
                                                                                                                                                                                                                                                                                                                                                                                                                                                                                                                                                                                                                                                                                                                                                                                                                                                                                                                                                                                                                                                                                                                                                                                                                                                                                                                                                                                                                                                                                                             |
| Study duration | 
60 months
                                                                                                                                                                                                                                                                                                                                                                                                                                                                                                                                                                                                                                                                                                                                                                                                                                                                                                                                                                                                                                                                                                                                                                                                                                                                                                                                                                                                                                                                                                                                                                                                                                                                                                                                                                 |

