|                       | 
statin treatment (atorvastatin 80mg/d) and combined standard antiplatelet and delayed intensive statin treatment (atorvastatin 40mg/d) will be tested.
 
2) Secondary outcomes:
 
a. Kaplan-Meier curve will be used to simulate the cumulative risk of 90-day follow-up combined with secondary endpoint events such as vascular events, ischemic stroke, TIA, myocardial infarction, vascular death and all-cause death. Cox proportional risk model will be used to calculate HR and the 95% confidence interval and the Log-rank test would be used to evaluate the efficacy;
 
b. For ordinal stroke or TIA, ordinal logistic regression will be used to calculate OR and 95% confidence interval. For the poor functional outcome (mRS score 2-6) and early neurological deficits (increase in NIHSS score at 7days) indexes, logistic regression will be used to calculate OR and 95% confidence interval.
 
c. Extreme values will be checked for validity and sensitivity analyses will be performed. A two-sided test will be used for all statistics, and <math>P < 0.05</math> is considered statistically significant.
 
3.3 Safety analysis
 
Safety evaluation will be analyzed using safety data set. Moderate to severe bleeding, intracranial hemorrhage, and overall mortality will be calculated using the Kaplan-Meier curve to simulate the 3-month cumulative risk, and the Cox proportional hazards model to calculate the HR and 95% confidence interval. For other adverse events and laboratory abnormalities, the cases which was normal before the treatment and abnormal after the treatment would be mainly analyzed and listed, in addition to the comparison of differences before and after treatment.
 |

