### 2.2 Secondary purposes:

**2.2.1** To evaluate the efficacy of intensive antiplatelet therapy versus standard antiplatelet therapy, immediate intensive statin therapy (atorvastatin 80mg/d) versus delayed intensive statin therapy

(atorvastatin 40mg/d), intensive antiplatelet therapy combined with immediate intensive statin therapy (atorvastatin 80mg/d) versus standard antiplatelet therapy combined with delayed intensive statin therapy respectively (atorvastatin 40mg/d) at 90 days in acute mild ischemic stroke or high-risk TIA patients attributed to intracranial or extracranial atherosclerosis on the incidence of (definitions shown in appendix 1, 2 and 5):

- Combined vascular events: stroke (ischemic or hemorrhagic), myocardial infarction, and cardiovascular death.
- Ischemic stroke
- TIA
- Severity of stroke or TIA on an ordinal scale: a six-level ordered category scale combined vascular events with mRS score at 90 days: fatal stroke (stroke with subsequent death), severe stroke (stroke followed by mRS of 4-5), moderate stroke (stroke followed by mRS of 2-3), mild stroke (stroke followed by mRS of 0-1), TIA, and no stroke/TIA
- Myocardial infarction
- Vascular death
- All-cause death
- Poor functional outcome (mRS score 2-6)
- Poor quality of life (EQ-5D scale index score  $\leq 0.5$ )

**2.2.2** To evaluate the efficacy in decreasing early neurological deficits (increase in NIHSS score at 7days), stroke recurrence, all-cause mortality and poor functional outcome (mRS score 2-6) at 1 year of intensive antiplatelet therapy versus standard antiplatelet therapy, immediate intensive statin therapy (atorvastatin 80mg/d) versus delayed intensive statin therapy (atorvastatin 40mg/d), intensive antiplatelet therapy combined with immediate intensive statin therapy (atorvastatin 80mg/d) versus standard antiplatelet therapy combined with delayed intensive statin therapy (atorvastatin 40mg/d) respectively in acute mild ischemic stroke or high-risk TIA patients attributed to intracranial or extracranial atherosclerosis. The new stroke or TIA is classified on a six-level ordered category scale combined vascular events with mRS score at 1 year: fatal stroke (stroke with subsequent death), severe stroke (stroke followed by mRS of 4-5), moderate stroke (stroke followed by mRS of 2-3), mild stroke (stroke followed by mRS of 0-1), TIA, and no stroke/TIA.

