### 4.2 Secondary outcomes:

- Combined vascular events : Stroke (ischemic or hemorrhagic), myocardial infarction, or cardiovascular death
- Ischemic stroke
- TIA
- Severity of stroke or TIA on an ordinal scale: (a six-level ordered category scale combined vascular events with mRS score: fatal stroke (stroke with subsequent death), severe stroke (stroke followed by mRS of 4-5), moderate stroke (stroke followed by mRS of 2-3), mild stroke (stroke followed by mRS of 0-1), TIA, and no stroke/TIA)
- Myocardial infarction
- Vascular death
- All-cause death
- Poor functional outcome (mRS score 2-6)
- Poor quality of life (EQ-5D scale index score  $\leq 0.5$ )
- Early neurological deficits (increase in NIHSS score at 7 days)

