### 16.1 Estimate Sample Size

The minimal sample size for the trial is determined by the necessity that a clinically meaningful difference in effectiveness between treatment and control groups has to be detected. Based on previous studies, the risk of new stroke during 90 days is presumed to be 11.5% in the group with standard antiplatelet therapy (with half delayed intensive statin therapy and half early high-intensity statin therapy) and 11.5% in the delayed intensive statin therapy group (with half standard antiplatelet therapy and half dual antiplatelet therapy) and 13% in the group with standard antiplatelet therapy plus delayed intensive statin therapy, intensive antiplatelet therapy and immediate intensive statin therapy can reduce this risk by 22%, and the effects of intensive antiplatelet and lipid lowering therapy will be similar and additive. With a sample size of 6100 subjects, a two-sided  $\alpha$  of 0.05 and 5% loss to follow up, we will have 97% power to detect that the risk is decreased by 35% in the group with dual antiplatelet therapy plus immediate intensive statin therapy compared to standard antiplatelet therapy plus delayed intensive therapy, and 80% power to detect that the risk is reduced by 20% by intensive antiplatelet therapy compared to standard antiplatelet therapy, and immediate intensive statin compared to delayed intensive statin therapy, respectively.

**Table1 For different risk rates (12% to 14%) of the results in the control group, the sample size required for observing intensive antiplatelet combining intensive statin therapy**

| Power | A single set of sample size (no expulsion) | A single set of sample size (5% expulsion rate) | Four groups of sample size | The stroke recurrence rate in treatment group | The stroke recurrence rate in control group | Relative risk |
|-------|--------------------------------------------|-------------------------------------------------|----------------------------|-----------------------------------------------|---------------------------------------------|---------------|
| 0.966 | 1448                                       | 1525                                            | 6100                       | 0.078                                         | 0.120                                       | 0.65          |

|       |      |      |      |       |       |      |
|-------|------|------|------|-------|-------|------|
| 0.975 | 1448 | 1525 | 6100 | 0.085 | 0.130 | 0.65 |

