#### 16.3.2.2 Efficacy analysis

- 1) Primary outcome:

Survival curves will be estimated for the primary outcome using the Kaplan-Meier procedure and compared using a Cox regression model Wald test, stratified by the opposite arm of the factorial design. First, marginal effects will be compared between intensive and standard antiplatelet therapy, and also between immediate intensive statin therapy (atorvastatin 80mg/d) and delayed intensive statin therapy (atorvastatin 40mg/d). As these are independent comparisons, they have no effect on the type I error rate. For both treatment comparisons, the primary outcome of stroke will be judged to be statistically significant if the treatment test p-value is  $< 0.05$ . Second, if either intensive antiplatelet or immediate intensive statin treatment (atorvastatin 80mg/d) is statistically significant, the effects between combined intensive antiplatelet and immediate intensive statin treatment (atorvastatin 80mg/d) and combined standard antiplatelet and delayed intensive statin treatment (atorvastatin 40mg/d) will be tested. Cox regression model stratified by the opposite arm of the factorial design, will be used in the curative effect assessment and evaluation between the subgroups.

- 2) Secondary outcomes:

- d. Kaplan-Meier curve will be used to simulate the cumulative risk of 90-day follow-up combined with secondary endpoint events such as vascular events, ischemic stroke, TIA, myocardial infarction, vascular death and all-cause death. Cox proportional risk model will be used to calculate HR and the 95% confidence interval and the Log-rank test would be used to evaluate the efficacy;
- e. For ordinal stroke or TIA, ordinal logistic regression will be used to calculate OR and 95% confidence interval. For the poor functional outcome (mRS score 2-6) and early neurological deficits (increase in NIHSS score at 7days) indexes, logistic regression will be used to calculate OR and 95% confidence interval.
- f. The validity of the extreme value would be examined, and the sensitivity analysis would be carried out.

- 3) Safety analysis

The overall of safety assessment is all used test medications and the safety follow-up case should be

recorded at least once. The safety evaluation data includes adverse reactions observed during the trial and changes in laboratory data before and after treatment.

Safety evaluation will be analyzed using safety data set.

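### The Summary's blanket P<0.05 rule covers ten secondary outcomes on three contrasts with no order, gate or exploratory label; one or more false nominal findings is about as likely as not, and one favouring the intensive arm about one in three

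*Supplement*

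**What the plan says.** All references are to protocol V4.0.

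- **Outcomes.** Section 4.2 lists ten secondary outcomes: combined vascular events, ischemic stroke, TIA, the ordinal stroke/TIA scale, myocardial infarction, vascular death, all-cause death, mRS 2-6, EQ-5D index at or below 0.5, and "Early neurological deficits (increase in NIHSS score at 7 days").
- **Contrasts.** Section 2.2.1 names the two marginal contrasts, "To evaluate the efficacy of intensive antiplatelet therapy versus standard antiplatelet therapy, immediate intensive statin therapy (atorvastatin 80mg/d) versus delayed intensive statin therapy", and then the combination "versus standard antiplatelet therapy combined with delayed intensive statin therapy respectively (atorvastatin 40mg/d) at 90 days". It lists nine of the ten outcomes. The tenth, early neurological deficit, is in section 2.2.2 on the same three contrasts.
- **One-year aims.** Section 2.2.2 also asks about "stroke recurrence, all-cause mortality and poor functional outcome (mRS score 2-6) at 1 year", plus the ordinal scale at one year.
- **Decision rule.** In the Summary, Statistical analysis 3.2, the part on secondary outcomes ends with "A two-sided test will be used for all statistics" and the P<0.05 threshold. The Summary's statistics section opens with the same threshold.
- **Purpose of the tests.** For the secondary time-to-event outcomes, section 16.3.2.2 says "the Log-rank test would be used to evaluate the efficacy".
- **Gate.** The only conditional step is for the primary outcome: "Second, if either intensive antiplatelet or immediate intensive statin treatment (atorvastatin 80mg/d) is statistically significant, the effects between combined" arms are compared. Nothing similar is written for secondary outcomes.

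**The concern.** The protocol gives thought to error rates for the primary outcome: it comments on type I error for the two marginal tests and makes the combination test conditional. For secondary outcomes it applies the same 0.05 threshold to every comparison and describes the log-rank tests as evaluations of efficacy. A reader of the eventual report could not tell which secondary P values were meant to support a claim. Under the written rule, a secondary outcome could be called statistically significant for a factor whose stroke comparison had failed. The chance that at least one such label is false is far above the level attached to any single test.

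**Working it through.** **The plan's own figures.** The plan gives no family-wise error rate for the secondary outcomes. The 0.05 level it does give is per comparison: section 16.1 assumes a two-sided α "of 0.05 and 5% loss to follow up, we will have 97% power". Its marginal power in Table 2 (0.807; 2896 per arm; 0.0930 vs 0.1157) reproduces with an unsplit 0.05 in a pooled two-proportion test:

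- Null SE = √(2 × 0.10435 × 0.89565 / 2896) = 0.00803.
- Alternative SE = √((0.0930 × 0.9070 + 0.1157 × 0.8843) / 2896) = 0.00803.
- (0.0227 − 1.96 × 0.00803) / 0.00803 ≈ 0.87, which gives power 0.807.

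**Number of comparisons.** 10 outcomes × 3 contrasts = 30. The one-year aims are left out because section 16.3.2.2 describes no analysis of them.

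**Upper figure, treating the 30 as independent.** Either direction: 1 − 0.95^30 = 78.5%. Favouring the intensive arm: 1 − 0.975^30 = 53.2%. Both are too high, because the comparisons are not independent.

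**Dependence between contrasts.** With four equal arms of n patients:

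- The antiplatelet contrast is (A+B)/2 − (C+D)/2 and the statin contrast is (A+C)/2 − (B+D)/2. They are uncorrelated, each with variance σ²/n.
- Their sum is A − D, with variance 2σ²/n. So z(A vs D) = (z₁ + z₂)/√2, which correlates 1/√2 = 0.71 with each marginal.

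**Dependence between outcomes.** Composite events, ischemic stroke and the ordinal scale share events. The documents give no correlations, so a common value ρ was varied.

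**Result.** 200,000 simulated trials per setting, no effect of either factor, critical value 1.96, at least one false result among 10 outcomes × 3 contrasts:

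| ρ (assumed) | Either direction | Favouring intensive arm |
|---|---|---|
| 0 | 70% | 45% |
| 0.2 | 67% | 39% |
| 0.4 | 59% | 33% |
| 0.5 | 54% | 29% |
| 0.6 | 49% | 26% |
| 0.8 | 35% | 18% |

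For one factor alone (10 outcomes), the corresponding ranges are 17-40% and 9-22%.

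**Checks.**

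- The protocol gives no analysis method for the EQ-5D outcome. Without it, nine outcomes on three contrasts give 34-67% in either direction and 18-42% in the favourable direction.
- A patient-level 2×2 simulation (4,000 runs, 1525 per arm, simple score tests in place of the log-rank and logistic models, assumed event rates) gave 58% in either direction and 34% in the favourable direction. For the two marginal contrasts only, it gave 53% and 31%.

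**Effect of a gate.** If a factor's secondary outcomes may be claimed only after its own stroke test is significant, the chance of any false claim over the two marginals, with no effects anywhere, is at most 1 − 0.95² = 9.75%. Counting only the favourable direction it is at most 1 − 0.975² = 4.9%.

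**The case against.** The strongest reply is that ordering or labelling secondary outcomes belongs in the analysis plan. Section 16.3 calls itself an overview and defers the planned analyses to a SAP due before database lock, which is not among the documents. That SAP may set a hierarchy, so nobody can say that the trial will lack one. If the protocol had said nothing on the point, this reply would settle it. But the protocol states a threshold in its Summary, in the part on secondary outcomes, and nothing in section 16.3.2.2 overrides it. The point is therefore limited to the protocol's own rule.

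Several stronger readings are tempting, and the documents do not support them:

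- **That a false efficacy claim is about as likely as not.** The 35-70% counts results in either direction, including those against the intensive arm. An efficacy claim needs a favourable result, for which the range is 18-45%.
- **That 42 tests are planned.** Adding four one-year outcomes on three contrasts (30 + 12) counts objectives. Section 16.3.2.2 describes no one-year analyses.
- **That a factor failing on stroke could be declared effective overall.** All three null hypotheses concern new stroke within 90 days, and stroke is the only primary outcome. The rule permits a label of significance on a secondary outcome and no more.
- **That section 16.3.2.2 repeats the rule.** Its only P<0.05 statement is for the primary outcome. The blanket rule is in the Summary.

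It is also true that the logistic and ordinal outcomes are promised only an odds ratio with an interval, although the Summary's threshold for all statistics still reaches them.

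**Conclusion.** The concern holds for the text of V4.0: ten secondary outcomes on three contrasts, a flat two-sided P<0.05, and no order, gate, adjustment or exploratory label. With no true effects, at least one false nominal P<0.05 has a chance of about 35-70%, or 7 to 14 times the 5% of a single test. One favouring the intensive arm has a chance of about 18-45%, roughly one in three, or about 7 to 18 times the 2.5% of a single test.

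These figures rest on assumed between-outcome correlations from 0 to 0.8 and on every null being true. The patient-level check also rests on assumed event rates. The conclusion does not depend on where in the range the truth lies. The primary analysis is unaffected; only the standing of secondary claims is. The change should be made, and the unseen SAP may already contain it.

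**What to change.** In the Summary, remove the P<0.05 significance rule for secondary outcomes. State there and in section 16.3.2.2, item 2), that secondary outcomes are exploratory and are reported as HR or OR with 95% CI and no claim of significance.

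If the sponsor wants to keep some secondary claims, allow them only for a factor whose own primary stroke test is significant. Test in an order that the sponsor fixes before database lock, and stop at the first non-significant result. Label the combination-contrast and one-year outcomes exploratory. The order is for the sponsor to choose.

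Either version is a wording change in the protocol and SAP and needs no new data or patients. All estimates and intervals are still reported. The cost is that fewer secondary results can be called statistically significant.

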## INSPIRES Abbreviated Vocabulary

| Abbreviation            | Interpretation                                                                                                                                                  |
|-------------------------|-----------------------------------------------------------------------------------------------------------------------------------------------------------------|
| ABCD  score | To predict risk of stroke within 2 days after the onset of transient ischemic attack (TIA), and to predict the recurrence risk of mild stroke in the short term |
| ACEI                    | Angiotensin-converting enzyme inhibitor                                                                                                                         |
| AE                      | Adverse event                                                                                                                                                   |
| ALT                     | Alanine aminotransferase                                                                                                                                        |
| ARB                     | Angiotensin-receptor blocker                                                                                                                                    |
| ASA                     | Aspirin, Acetylsalicylic acid                                                                                                                                   |
| ASSORT                  | Administration of Statin on Acute Ischemic Stroke Patient                                                                                                       |
| AST                     | Aspartate aminotransferase                                                                                                                                      |
| BP                      | Blood pressure                                                                                                                                                  |
| CABG                    | Coronary artery bypass graft                                                                                                                                    |
| CEMRA                   | Contrast-enhanced magnetic resonance angiography                                                                                                                |
| CHANCE                  | Clopidogrel in high-risk patients with acute non-disabling cerebrovascular events                                                                               |
| CI                      | Confidence interval                                                                                                                                             |
| CK                      | Creatine kinase                                                                                                                                                 |
| CLAIR                   | Clopidogrel plus aspirin versus aspirin alone for reducing embolisation in patients with acute symptomatic cerebral or carotid artery stenosis                  |
| COMPRESS                | Combination of Clopidogrel and Aspirin for Prevention of Recurrence in Acute Atherothrombotic Stroke Study                                                      |
| CRF                     | Case report form                                                                                                                                                |
| CRO                     | Contract Research Organization                                                                                                                                  |
| CT                      | Computed Tomography                                                                                                                                             |
| CTA                     | Computed tomography angiography                                                                                                                                 |

|          |                                                                                                     |
|----------|-----------------------------------------------------------------------------------------------------|
| CYP2C19  | Cytochrome P450, family2, subfamily C, polypeptide 19                                               |
| CYP3A    | Cytochrome P450, family 3, subfamily A                                                              |
| DSA      | Digital subtraction angiography                                                                     |
| DSMB     | Data and Safety Monitoring Board                                                                    |
| DWI      | Diffusion-weighted imaging                                                                          |
| EQ-5D    | EuroQoL-5 Dimensions                                                                                |
| GUSTO    | Global Utilization of Streptokinase and Tissue Plasminogen Activator for Occluded Coronary Arteries |
| HR       | Hazard ratio                                                                                        |
| ICH      | Intracerebral hemorrhage                                                                            |
| IRB      | Institutional Review Board                                                                          |
| LDL-C    | Low-density lipoprotein cholesterol                                                                 |
| MRA      | Magnetic resonance angiography                                                                      |
| MRI      | Magnetic resonance imaging                                                                          |
| mRS      | Modified Rankin Scale                                                                               |
| NIHSS    | National Institute of Health Stroke Scale                                                           |
| NASCET   | North American Symptomatic Carotid Endarterectomy Trial                                             |
| OR       | Odds ratio                                                                                          |
| PPI      | Proton-pump inhibitor                                                                               |
| rt-PA    | Recombinant tissue-type plasminogen activator                                                       |
| SAE      | Serious adverse event                                                                               |
| SAH      | Subarachnoid hemorrhage                                                                             |
| SAMMPRIS | Stenting and Aggressive Medical Management for Preventing Recurrent Stroke in Intracranial Stenosis |
| SPARCL   | Stroke Prevention by Aggressive Reduction in Cholesterol Levels                                     |

[figure not shown]

|       |                                                         |
|-------|---------------------------------------------------------|
| TCD   | Transcranial doppler                                    |
| WASID | Warfarin - Aspirin for Symptomatic Intracranial Disease |

